#### 2.6.3. Secondary Outcomes

Secondary outcomes are listed as the changes of body mass index (BMI), waist perimeter and hip perimeter, waist-hip ratio, blood lipids (total cholesterol (TC), triglyceride (TG), low-density lipoprotein cholesterol (LDL-C), and high-density lipoprotein cholesterol (HDL-C)), blood pressure, carotic artery intima-media thickness, and improvement in TCM symptoms (evaluated by TCM symptom score scale). Blood pressure, carotic artery intima-media thickness, and TCM symptom score are evaluated every 12 weeks, and the remaining indexes are evaluated every 4 weeks.

#### 2.6.4. Safety Assessment

Vital signs (body temperature, blood pressure, respiration, and heart rate), electrocardiogram (ECG), routine blood test, routine urine test, and routine stool test are evaluated at baseline and week 24Liver function including alanine aminotransferase (ALT) and aspartate aminotransferase (AST) and renal function, including serum creatinine (SCr) and blood urea nitrogen (BUN), at baseline and week 24

#### 2.6.5. Questionnaires

Lifestyle intervention is measured using the questionnaire. During the period of intervention, the study participants will be asked to fill in a diary describing the intake of staple food and meals consumed every day. In addition, the participants are asked to weigh every week and register the type and duration of physical activity.

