## 2. Methods

### 2.1. Trial Design

This study is a multicenter cohort study with two arms. A total of 600 participants will be recruited. The participants will be divided into either intervention or control groups according to their own desire, and the exposure factor is the application of TCPMs. All participants will be encouraged to lead a healthy lifestyle, and the intervention group also used TCPMs based on syndrome differentiation. Incident diabetes and normalization of blood glucose are indexes of end point. Safety assessments and adverse event monitoring will also be conducted. The treatment duration is set for 24 weeks, and we will follow-up for another 2 years.

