#### 2.5.1. Lifestyle Intervention

The guidelines for the prevention and treatment of type 2 diabetes (2017 edition) suggest that subjects with abnormal glucose metabolism should reduce their risk of T2DM through controlling diet and strengthening exercise. Lifestyle intervention will be implemented by medical staff, and a health management application will be used. Firstly, healthy lifestyle education will be developed every 2 weeks. The aim of the education is to promote changes in lifestyle behaviors strongly associated to overweight/obesity and the risk of T2DM and to provide personalized health behavior guidance for different target groups. Secondly, the trial will advocate a healthy reasonable match of calories, carbohydrates and protein, and low-salt low-fat and low-sugar diet. The staple food is suggested to be quantitative with the combination of coarse food grain and wheat flour and rice, the daily consumption of vegetables should be enhanced, regular intake of fish and poultry is suggested, appropriate intake of eggs and livestock meat and limited intake of processed meats is suggested, and the intake of sugar, sugar-sweetened beverages, and energy-dense foods is suggested to be reduced. Thirdly, physical activity of moderate intensity, such as brisk walking, swimming, tai chi, and eight-section brocade, is engaged for at least 150 minutes per week. Through the lifestyle interventions mentioned above, the goal for overweight/obese participants is 5–10% of weight reduction in 6–8 months.

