### 2.7. Study Visits and Data Collection

The study is divided into two periods, a 24-week drug intervention period and a 24-month follow-up period. After the intervention period commences, telephone visits will take place every 2 weeks and outpatient visits every 4 weeks. When the follow-up period commences, outpatient visits will take place every 6 months. An overview of data capture can be found listed in Table 1.

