## Figures and Tables

**Figure 1 fig1:**
[figure not shown]
Flow diagram of enrollment, intervention, and assessments.

**Table 1 tab1:** Schedule of enrollment, allocation, visits, and assessments.

Time of visits	Enrolment	Allocation	Drug intervention period				Follow-up period			
	−2w	0w	4w, 8w	12w	16w, 20w	24w	12 m	18 m	24 m	30 m
*Collect basic medical history*										
Sign informed consent form	√									
Determine inclusion and exclusion criteria	√	√								
Determine withdrawal criteria	√	√	√	√	√	√	√	√	√	√
Fill in general information	√	√								
History of prediabetes and treatment	√									
Comorbidity and symptom	√									
Physical examination and consultation	√	√	√	√	√	√	√	√	√	√
Concomitant medication	√	√	√	√	√	√	√	√	√	√

*Efficacy assessment*										
Glycosylated hemoglobin		√		√		√	√	√	√	√
Fasting plasma glucose		√	√	√	√	√	√	√	√	√
2-hour postprandial blood glucose		√	√	√	√	√	√	√	√	√
Blood lipids		√		√		√	√	√	√	√
Carotic artery intima-media thickness		√		√		√	√	√	√	√
BMI, waist perimeter and hip perimeter, waist-hip ratio, and blood pressure		√	√	√	√	√	√	√	√	√
TCM symptom score		√		√		√	√	√	√	√

*Safety assessment*										
Vital signs		√				√	√	√	√	√
Routine blood, urine, and stool examination		√				√	√	√	√	√
Liver function		√				√	√	√	√	√
Renal function		√				√	√	√	√	√
Electrocardiogram		√				√	√	√	√	√
Hypoglycemic episodes			√	√	√	√	√	√	√	√
Adverse events			√	√	√	√	√	√	√	√

*Other work*										
Record of TCPMs		√	√	√	√	√	√	√	√	√
Research summary						√				√

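### No pre-choice measure of diet or physical activity is scheduled, although participants choose their own arm and the comparison is unadjusted

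*Protocol article*

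**What the plan says.** Section 2.1 forms the arms by preference: "The participants will be divided into either intervention or control groups according to their own desire". Table 1 puts allocation in the week-0 column, after an enrolment visit at −2 weeks.

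Section 2.6.5 is the section on lifestyle measurement. It names three instruments:

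- A questionnaire, with no visit or period attached: "Lifestyle intervention is measured using the questionnaire".
- A diet diary with a stated window: "During the period of intervention, the study participants will be asked to fill in a diary describing the intake of staple food and meals consumed" each day.
- A log, introduced as an addition to the diary and with no window of its own: "the participants are asked to weigh every week and register the type and duration of physical activity".

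Section 2.7 divides the study into "a 24-week drug intervention period and a 24-month follow-up period" and refers the reader to the schedule: "An overview of data capture can be found listed in Table 1". That table has no row for diet, physical activity, diary or lifestyle questionnaire at any visit.

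Section 2.4.3 requires a month of diet and exercise before entry but mentions no recording of it. Section 2.11 compares the groups with chi-square, t, Fisher's exact and rank sum tests, and states no adjustment.

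**The concern.** Where people pick their own treatment, the groups can differ beforehand in whatever drives both the choice and the outcome. Lifestyle is an obvious candidate here. Section 2.5.1 links the targeted behaviours to diabetes risk, the Discussion says that current prevention rests mainly on improving lifestyle, and lifestyle intervention is the background treatment in both arms. Those who opt for the patent medicines may be more health-conscious, or they may want a medicine because they are less willing to change their diet.

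A diary that begins after an open, self-chosen allocation cannot stand in for a baseline. What participants eat and do from then on may respond to the arm they chose, so adjusting for it conditions on a post-exposure variable.

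Timing makes this more than a matter for the analysis plan. A later plan can add a regression model or a propensity score, but it cannot recover a baseline that was never collected.

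**Working it through.** The plan gives no figure on this point to reproduce. The check is a reading of the schedule, followed by an illustration of size.

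**Step 1: timing of each lifestyle measure against the choice of arm (week 0)**

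| Item | Stated timing | Before the choice? |
|---|---|---|
| Diet diary (2.6.5) | Intervention period | No |
| Weight and activity log (2.6.5) | None of its own; described alongside the diary | Not stated; read in context, no |
| Lifestyle questionnaire (2.6.5) | None | Not stated |
| Run-in month (2.4.3) | Before entry | Yes, but no recording is described |
| Table 1, −2 weeks and week 0 | No lifestyle row | No |
| Table 1, week 0: BMI, waist, hip, blood pressure, lipids, glucose, HbA1c | Week 0 | On the allocation day, but these are proxies |

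No pre-choice measure of diet or activity is scheduled anywhere in the document.

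**Step 2: how large a bias could follow**

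The documents give neither the strength of the lifestyle effect nor its distribution by arm, so these are assumptions. For one binary factor and no true treatment effect, the spurious risk ratio is

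(pT × RR + 1 − pT) / (pC × RR + 1 − pC),

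where pT and pC are the proportions with low activity among those choosing the patent medicines and among controls.

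Assume RR = 2 and pC = 0.5. The denominator is 0.5 × 2 + 0.5 = 1.5.

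- pT = 0.3: (0.6 + 0.7)/1.5 = 1.3/1.5 = 0.87
- pT = 0.4: (0.8 + 0.6)/1.5 = 1.4/1.5 = 0.93
- pT = 0.6: (1.2 + 0.4)/1.5 = 1.6/1.5 = 1.07
- pT = 0.7: (1.4 + 0.3)/1.5 = 1.7/1.5 = 1.13

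A wider imbalance, also assumed: let a good lifestyle carry a relative risk of 0.4 to 0.6, with prevalence 70% against 30% in favour of the patent-medicine arm.

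- Relative risk 0.4: (0.7 × 0.4 + 0.3)/(0.3 × 0.4 + 0.7) = 0.58/0.82 = 0.71
- Relative risk 0.6: (0.7 × 0.6 + 0.3)/(0.3 × 0.6 + 0.7) = 0.72/0.88 = 0.82

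With the prevalences exchanged, the ratios are the reciprocals: 0.82/0.58 = 1.41 and 0.88/0.72 = 1.22.

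**Step 3: set against the planned effect**

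Section 2.10 assumes annual conversion of 5.7% against 10%, a ratio of 5.7/10 = 0.57. On the log scale, ln(0.57) = −0.562. A spurious ratio of 0.87 (ln = −0.143) is 0.143/0.562 = 25% of the planned effect, and 0.93 (ln = −0.069) is 0.069/0.562 = 12%. In all of these ranges the bias could create or hide part of the planned effect, but not create all of it.

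**The case against.** The strongest reply is that the document does not say lifestyle goes unrecorded before the choice. Only the diet diary has an explicit window. Table 1 also omits the diary during weeks 4 to 24, when Section 2.6.5 says it is kept, so the table's silence is weak evidence. Its general-information row at −2 weeks and week 0 could hold lifestyle items, and case report form content is commonly left to a full protocol. This stands against a flat claim that lifestyle is recorded only during treatment, which a reader might infer. It does not remove the point: the one window the document does fix begins after the choice, and nothing it states provides an earlier measure.

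Second, baseline BMI, waist, lipids and glucose are scheduled, and all entrants have completed a month of diet and exercise and still meet the glucose criterion. An adjusted analysis could therefore remove some of the confounding. This also stands. It would be too strong to say that adjustment is futile without a lifestyle baseline; what remains is the part of lifestyle that these proxies miss.

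Third, a reader might infer that lifestyle must be tracked to 30 months so that late differences can be adjusted for it. Such data are post-exposure, just as the treatment-period diary is, and are useful for description only.

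Fourth, a reader might add that the weight target ("the goal for overweight/obese participants is 5–10% of weight reduction in 6–8 months") falls between visits. The document does not support this. The Discussion treats the 24-week treatment as six months, and the follow-up visits at 12, 18, 24 and 30 months fit that calendar, so the window opens at an existing visit. No listed outcome uses the target.

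**Conclusion.** The point holds as a gap in scheduled data collection: the arms are self-chosen, lifestyle is central to the plan's own reasoning, and no diet or activity measure is scheduled before the choice. Neither the direction nor the size of the bias can be derived from the document. Under the main assumptions (relative risk 2, 50% low activity in controls) the spurious risk ratio is 0.87–0.93 or 1.07–1.13, depending on who chooses the patent medicines, against a planned 0.57. The documents do not support a claim that the bias favours the patent medicines, or that it could account for the whole planned effect. The illustration concerns incident diabetes; no size is derived for the glucose and HbA1c outcomes. This should be corrected because it is cheap now and cannot be repaired once participants have chosen.

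**What to change.** - **Section 2.6.5 and Table 1:** give the existing questionnaire, diary and activity log at the −2-week enrolment visit, and add the corresponding row. Summarise them at week 0, before the participant states a choice of arm. The run-in lasts a month, so it may already be under way at −2 weeks. The questionnaire should therefore also ask about habits before the run-in where possible; otherwise the baseline reflects instructed behaviour.
- **Section 2.11:** add an adjusted between-group comparison that includes the pre-choice lifestyle summary, either as a covariate or in a propensity score, together with the clinical baseline values already scheduled.
- **Optional:** repeat the short questionnaire at the existing 12, 18, 24 and 30-month visits, and state that these values are descriptive and will not be used for adjustment.

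No new visit or instrument is needed. The cost is an amendment to two sections and the table, a few more weeks of diary keeping, and some added data entry. Recall of habits before the run-in will be imperfect. Adjustment would still leave unmeasured reasons for the choice uncontrolled.

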### 2.7. Study Visits and Data Collection

The study is divided into two periods, a 24-week drug intervention period and a 24-month follow-up period. After the intervention period commences, telephone visits will take place every 2 weeks and outpatient visits every 4 weeks. When the follow-up period commences, outpatient visits will take place every 6 months. An overview of data capture can be found listed in Table 1.

### 2.8. Adverse Event Monitoring

Any adverse events (AEs), such as subjective discomfort of participants and abnormal laboratory tests, should be treated seriously, analyzed carefully, and addressed immediately. An adverse event report form will be recorded at every visit, including the occurrence time, severity, duration, adopted measure, and transfer. Every AE will be classified as a mild, moderate, or severe AE, and its relationship between AEs and the intervention drugs will be judged: whether the reasonable relationship exists between the time of drug use and the occurrence of suspicious AEs; whether the suspected AEs conform to the known adverse reactions of the drug; whether the suspicious AEs can be explained by the effect of combined drugs, the clinical condition of patients, or the effect of other therapies; whether the suspected AEs will disappear or alleviate after drug withdrawal or dosage reduction; and whether the same AEs will occur again after reexposure to intervention drugs. Severe AEs will be reported to the principal investigator and the Ethics Committee immediately, and the “Severe Adverse Event (SAE)” form is filled out. The severe adverse events should also be reported to the safety supervision division of the State Food and Drug Administration within 24 hours. All AEs must be treated until properly resolved, retested in 24 hours, 7 days, and 14 days according to the situation, informed the clinical supervisor of the results, and tracked until they are stable.

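### Section 2.8 uses the word severe both as the top adverse event grade and as the only trigger for expedited reporting, and seriousness is nowhere defined

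*Protocol article*

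**What the plan says.** All the relevant text is in section 2.8 (Adverse Event Monitoring) of the protocol article.

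- Classification: "Every AE will be classified as a mild, moderate, or severe AE". Apart from the judgement of relatedness to the drug, this is the only classification of AEs in the article.
- Report to the principal investigator and ethics committee: "Severe AEs will be reported to the principal investigator and the Ethics Committee immediately". The same sentence calls for the SAE form, whose name spells out the S as *severe*.
- Report to the regulator: "The severe adverse events should also be reported to the safety supervision division of the State Food and Drug Administration within 24 hours".
- Routine recording: "An adverse event report form will be recorded at every visit, including the occurrence time, severity, duration, adopted measure, and transfer". Severity is among the listed items; seriousness is not.
- Handling of all AEs: they "should be treated seriously, analyzed carefully, and addressed immediately". They are also followed until stable, with results passed to the clinical supervisor.

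**The concern.** How intense an event is and how serious its consequences are differ as attributes. An event of moderate intensity can lead to hospital admission, and an intense symptom can pass without consequence. Expedited reporting exists to bring events with grave outcomes quickly to those who can act on them, so its trigger should rest on outcome. Here the trigger is the word that has just been used for the top of a three-step grade.

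The stake is which events reach the ethics committee and the regulator promptly. Safety is a stated aim in the Abstract and the Background. Section 2.7 sets outpatient visits every 4 weeks during treatment but only every 6 months during the 24-month follow-up, so routine recording at visits is a slow route for most of the study. Participants also choose their own group (section 2.1) and there is no placebo (Discussion). A graded judgement of how bad an event is can therefore be influenced by knowing the treatment, more easily than a fact such as admission or death.

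**Working it through.** No arithmetic applies. The check is to set the sentences of section 2.8 side by side, work out what they imply, and look elsewhere in the article for anything that changes the result.

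**Step 1: the triggers.** Three expedited actions are stated: the immediate report to the principal investigator and ethics committee, the SAE form, and the 24-hour regulator report. All three depend on the word *severe*, and no other trigger is given.

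**Step 2: what the word means in that section.** It appears first as the top step of the mild, moderate, severe classification, and the trigger sentences follow in the same paragraph without a new definition. The natural reading is that the same category is meant.

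**Step 3: consequence of that reading.** Cross the grade with the outcome, taking *serious* in its usual outcome-based sense:

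| Grade | Outcome | Expedited under section 2.8 as written | Expedited if the trigger were seriousness |
|---|---|---|---|
| Severe | Serious | Yes | Yes |
| Severe | Not serious | Yes | No |
| Mild or moderate | Serious | No | Yes |
| Mild or moderate | Not serious | No | No |

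The two rules agree in the first and last rows and differ in the middle two. The third row matters for patient safety. The second adds reports of little value.

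**Step 4: search for a correction elsewhere.** No section uses the term serious adverse event, and none lists death, threat to life, hospital admission, disability or a similar outcome as a reporting criterion. The nearest wording is in the first sentence of section 2.8 ("should be treated seriously, analyzed carefully, and addressed immediately"), which concerns how AEs are handled. Section 2.11 says that adverse events and laboratory results are assessed in the safety set, but does not touch reporting. Table 1 schedules AE recording at each visit and gives no trigger.

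**Step 5: what happens to events graded lower.** They are recorded at visits, treated, retested as needed and followed, and the clinical supervisor is told the results. No expedited report to the ethics committee or the regulator is stated for them.

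**The case against.** The strongest reply is that this is a terminology slip in a condensed article. The abbreviation SAE, a dedicated form and a 24-hour regulator report all belong to the usual handling of *serious* events. The article is loose with standard terms elsewhere: section 2.2 abbreviates informed consent forms as CRFs, which section 2.9 uses for the case report form, and section 2.11 speaks of randomized participants in a study where people choose their group. *Severe* is also used broadly for grave conditions in sections 2.4.4 and 2.4.5. This stands as an explanation. A reader might infer that the sponsor deliberately chose intensity as the trigger, or that translation cannot account for the wording; the document supports neither. A slip in a reporting rule still needs correcting, because anyone working from this text has no other definition.

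A second reply is that seriousness criteria are often left to the full protocol, the SAE form or the operating procedures that section 2.12.2 mentions. That would excuse leaving out the list. It does not excuse a trigger that the article states outright and attaches to a grade. It does limit what can be said about the forms: the AE form is not shown, and its contents are introduced as a list of inclusions, so it may already hold a seriousness item.

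A third reply is that section 2.8 never defines the grades or calls them intensity, and that all AEs are to be addressed at once and followed. Both points are true. Events graded lower are not lost from the safety data, but following them up is not the same as reporting them to the ethics committee or regulator.

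**Conclusion.** The point holds as a defect in a stated rule. Section 2.8 makes one word serve as both grade and trigger, and followed literally it would route some events wrongly in both directions.

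The size cannot be given as a number, because the document has no AE rates or grade distributions. In scope, it covers every event with a serious outcome that is graded mild or moderate, and every event graded severe without a serious outcome. This assumes that the grades carry their usual meaning of intensity. If an unseen definition put every event with a serious outcome into the severe grade, the first of these groups would be empty.

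Two stronger readings are tempting and are not supported. A reader might infer that grave events will in fact go unreported, but the article shows only what its wording requires, not what sites will do. A reader might also infer that the label decides an SAE comparison in the final analysis, but section 2.11 states no such comparison. The primary outcome, the sample size and the efficacy analysis are unaffected.

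**What to change.** In section 2.8:

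1. Replace the trigger with *serious adverse event*, defined by the standard outcome criteria: death, threat to life, hospital admission or its prolongation, lasting disability, or birth defect.
2. Attach the SAE form, the immediate report to the principal investigator and ethics committee, and the 24-hour regulator report to that definition, and rename the form to match.
3. Make sure the AE form records seriousness as an item separate from severity.
4. Keep mild, moderate and severe as a descriptive grade with no reporting consequence of its own.

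If the full protocol, form or operating procedures already define seriousness this way, the correction is confined to the wording of section 2.8. Otherwise it also needs one field on the AE form and a matching line in the site procedures. Neither changes the design, the visit schedule or the analysis.
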